## Abstract

**Background:**

Art psychotherapy has greater potential for use with adults with mild to moderate learning disabilities as it places less of a burden on verbal interaction to achieve positive therapeutic, psychological, and behavioural goals. The feasibility study objectives include testing procedures, outcomes, validated tools, recruitment and attrition rates, acceptability, and treatment fidelity for manualised interpersonal art psychotherapy.

**Methods:**

Adult males and females with mild to moderate learning disabilities will be recruited from four NHS secure hospitals. Twenty patients will be recruited and randomly assigned to one of two treatment groups: fifteen 1-h individual sessions of manualised interpersonal art psychotherapy, or a treatment as usual waiting list control group. The Modified Overt Aggression Scale will be administered to both treatment arms. Four patients will be recruited to a single-case design component of the study exploring the acceptability of an attentional condition.

**Discussion:**

This multi-site study will assist in future trial planning and inform feasibility including, procedures, treatment acceptability, therapist adherence, and estimation of samples size for a definitive RCT.

**Electronic supplementary material:**

The online version of this article (10.1186/s40814-017-0186-z) contains supplementary material, which is available to authorized users.

## Background

Art therapies, such as art psychotherapy, are currently used in a range of NHS healthcare settings. They are included in the UK National Institute for Health and Care Excellence (NICE) adult and children and young people’s guidelines for psychosis and schizophrenia and the guidelines for the treatment of depression in children and young people [1–3]. Although art therapy is included in NICE guidelines for psychosis and schizophrenia in adults, a Cochrane review of art therapy [4] (two trials, *n* = 137) concluded that the evidence of benefits and harms was inconclusive.

A systematic narrative review of 15 trials [5] of group art therapy reported lower levels of anxiety and depression, including a study of incarcerated men. The art therapy trails reviewed were targeted at symptoms of depression, anxiety, low mood, trauma, distress, reduced QoL, low coping skills, and self-esteem [5]. However, the studies were generally considered to be of low quality and the need for future high-quality research in this area was identified [5, 6]. A systematic review of art therapy studies for traumatised adults found 6 clinical evaluations (*n* = 223) but just one RCT including art therapy plus cognitive behaviour therapy for victims of sexual assault and victims with post-traumatic stress disorder (PTSD (*n* = 8)) [7]. A realist review of art therapy for depression included 16 papers and identified 8 therapeutic factors that explained how art therapy works, including self-expression, communication, understanding, and creativity [8].

A review of art therapy literature for people with learning or intellectual disabilities [9] found one RCT. Art facilitation with adults (*n* = 19) showed a difference between language comprehension and social interaction for the treatment group against the control group with an analysis of covariance of post-test with pre-test scores as covariates (*p* < .10) [10].

For people with learning disabilities, art psychotherapy uses art media as its primary mode of communication and having artistic skill and experience in art is not a prerequisite. This can offer the opportunity for expression and communication in the context of a psychological therapy to people who find it hard to express their thoughts and feelings verbally [9]. Through focusing communication around visual material there is greater potential for people with a learning disability, limited English proficiency (LEP), and/or a mental health difficulties, to develop understanding about themselves/their health or behaviour/and what they can do to enhance their well-being [11].

In offender populations a meta-synthesis review of the role of art therapies in therapeutic goals identified associations with improvements in emotional literacy, quality of life, and lower levels of arousal linked with feelings of anger [12]. Examples of ‘proof of concept’ work in adult offenders with learning disabilities have indicated positive outcomes from art psychotherapy in single-case designs. Reported improvements included reduced levels of aggression after receiving up to twenty individual sessions of treatment [13–15]. This preliminary work has led to the development of a working manual for interpersonal art psychotherapy that is being considered in this study.

Development of health technology and therapeutic interventions that support a reduction in aggressive behaviour in adults with learning disabilities has potential for clinical benefits for patients in England. Data collected as part of a national learning disability census identified a population of 3230 adults with learning disabilities being treated in hospital with a total of 1780 patients (55%) having one or more recorded incident of self-harm, accidents, physical assault, restraint, or seclusion (either ‘present’ or ‘severe’ enough risk to require hospital treatment). Within this group of patients, 5460 separate types of risk were recorded for either violence, self-injury, or damage to property [16]. An international literature review of inpatient violence and aggression [17] reported that patients treated in forensic settings are likely to be more violent than those in other settings such as psychiatric units.

Future art therapy trials could mitigate potential performance bias through being allocated to the active treatment group and assess the relative efficacy of art therapy using an attention art-based placebo control to ensure that groups are treated equally [5]. In an attempt to explore a possible comparator for a future trial, the acceptability of an attentional control condition will be tested using a single-case design [18] in parallel to the randomised waiting list control study.

In an attentional condition the level of time and attention given to the participant should match that of the treatment (structural equivalence of dose) and have a rationale for therapeutic benefit [19]. Relaxation therapy to treat symptoms of anxiety is identified as specific psychological intervention that can be considered with adults with learning disability and mental health problems [20].The attentional condition being tested is mindful colouring-in for relaxation. Adult art therapy, mindful, and relaxation colouring-in books are now widely available to purchase as a self-help resource.

## Methods/design

### Study aims and objectives

The aim of the study is to establish the feasibility of conducting a definitive RCT of interpersonal art psychotherapy, with a primary focus on implementation and acceptability. The feasibility study will be carried out in four NHS secure hospital sites in England with treatment being provided by trained art psychotherapists who are registered with the UK Health and Care Professions Council (HCPC).

The study objectives for the assessment of feasibility are:Recruitment and consent, such as patients willingness to be randomised and clinicians willingness to recruit their patients into the study.Identifying issues related to seeking informed consent and risks of coercion, including potential for patients to participate in the study believing it will positively or negatively influence their inpatient treatment or detention under the mental health act.Procedures and materials, including suitability of study information, suitability of outcome measures, appraising burden of outcome measures and validated tools and suitability of outcome data collection procedures for maintaining data integrity from multiple study sites.Describing routine care and treatment as usual, identifying characteristics of treatment as usual across multiple sites, levels of high and medium/low security, and individualised patient care pathways.Attrition and acceptability, including rates of attendance for treatment and the acceptability of a novel attentional condition, reasons for non-attendance and/or drop-out, and lack of retention for data collection at the follow-up points.Identifying risks of contamination, such as patients on the waiting list receiving active components of the treatment during routine care and/or in the attentional condition.Treatment fidelity, identifying therapist adherence with the required activity in the treatment manual and piloting treatment fidelity checklist and procedures.

### Design

#### Waiting list control

This multi-centre feasibility study will utilise a parallel-group, participant-randomised design, with participants being allocated to either manualised interpersonal art psychotherapy and treatment as usual, or treatment as usual only while being placed on a waiting list for interpersonal art psychotherapy.

#### Single-case design

Four participants will be separately recruited to take part in single-case multiple-intervention ‘ABACA’ design studies [18] where measures are administered across ‘A’ = baseline (pre-therapy), ‘B’ = first treatment (mindful colouring-in attentional condition), ‘A’ = baseline (wash out period), ‘C’ = second treatment (interpersonal art psychotherapy), ‘A’ = baseline (post-therapy).

#### Client interviews

A brief post-therapy semi-structured interview will be carried out with participants. Questioning will explore helpful and unhelpful aspects of therapy and the participant’s experience of taking part in the study.

#### Treatment fidelity and contamination

Audio recordings from all therapy sessions will be collected. A random sample of 25% of recordings will be blind rated using a therapy checklist by a researcher independent of all other aspects of the study. This assessment will test treatment differentiation (did the providers only deliver the target treatment and not other treatments), treatment competency (did providers maintain the skill set learned in training), and treatment adherence (delivery of the treatment components as intended) [21]. The same procedure will be repeated for audio recordings of the attentional condition to check for presence or absence of components that could constitute contamination from the manualised treatment.

### Intervention

#### Interpersonal art psychotherapy

Interpersonal art psychotherapy has been developed and manualised from practice-based evaluations [13–15]. Directions for the therapist, in terms of style, approach, and techniques, are given in detail in the manual. The interpersonal component of the treatment manual is informed by the core conflictual relationship theme approach [22].

Interpersonal art psychotherapy is delivered in 15 therapy sessions of up to 1 h. Four HCPC registered art psychotherapist (one in each site) have received a 2-day training in the use of the treatment manual. The typical structure of therapy sessions includes the therapist giving an introduction to the session content followed by a directed art activity and a discussion between the therapist and participant.

Including drawing tasks in sessions helps therapists and clients to remember what has been said or what the focus of a session was. Drawings can act as a helpful record that can be referred back to during the course of therapy. In clinical practice it has also been the case that the act of drawing in therapy sessions has prompted some people to remember details of an event they are trying to recall.

Initial therapy sessions focus on helping the patient to identify immediate problems followed by identifying their existing positive coping skills and how they are being used and/or introducing additional coping skills if needed. The patient is then asked to give accounts of their relationships and examples of social interactions. The patient is then asked to think about current or past events and draw pictures of them to aid discussion with the therapist. The content that has been elicited and discussed with the patient in the proceeding sessions is then used to develop or formulate a shared understanding with the patient about reoccurring themes in their accounts of interpersonal interactions that are strongly associated with conflict or aggression. Near the end of therapy, the patient is asked to look ahead and think about themselves in the future including their aspirations or specific personal goals. To end the therapy, a review of the content of all sessions takes place and the patient leaves with a personalised summary and closing letter from the therapist.

The session schedule is as follows: 1 to 3—identifying current problems and coping strategies; 4 to 5—relating to others; 6 to 10—personal life events; 11 to 12—interpersonal themes; 13 to 14—imagining the future; and 15—end of therapy review. The sessions focus on combined components to develop a shared understanding with the client about their dominant interpersonal styles of interacting with others. This includes raising awareness of themes related to the client’s underlying needs or ‘wish’ for particular responses from the people they are interacting with.

#### Attentional condition

Within the single-case design, an attentional condition will be provided. Participants are asked to complete 15 sessions of up to 1 h of mindful colouring-in. During the activity, participants will be given additional instructions by the therapist to breathe slowly and notice what they are doing ‘in the here and now’. Sessions will be delivered by a qualified art psychotherapist and will be equivalent in dose, in terms of number of sessions, to the manualised interpersonal art psychotherapy treatment. Criteria for assessing acceptability of the attentional condition in this study will include the participant’s perception of appropriateness of the intervention for addressing the target problem and willingness to adhere to treatment [23].

### Outcomes

#### Feasibility outcomes

Objective 1, willingness to be randomised and clinician’s willingness to recruit, will be evaluated by assessing the number of eligible patients who were recruited at each site and the number of patients who declined (Additional file 1). For objective 2, issues related to seeking informed consent and potential for coercion will be reported by locally based members of the research team. The same reporting process will be utilised for objective 3 with research assistants reporting feedback from patients at each data collection point on the burden of outcome questionnaires. The level of completion of questionnaires (instrument and item response rates) will be monitored within routine data integrity checks. Objective 4, describing routine care, will be carried out from reviewing individual patient treatment plans. Objective 5, monitoring attrition and acceptability, will be addressed by a combination of recording attendance to treatment and from post-therapy client interview reporting and retention for follow-up data collection. Objective 6, assessing contamination, will be met by crosschecking information collected for objective 5 and by using the treatment fidelity checklist being used to assess objective 7, therapist adherence to the manual, on a sample of audio recordings from the attentional control condition.

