##### Inclusion criteria for patients

An inpatient in a NHS secure hospital having been assessed with IQ of between 55 and 79 (within a range including moderate/mild/borderline intellectual disability). Age 18 to 60 years (within the age range for patients treated in the service) and able to give informed consent. Having a historic and continuing presentation of emotional control difficulties and/or observed aggression or antagonistic behaviour that puts the individual at odds with other people (as identified by the clinical team).The patient’s involvement in the study is supported by their responsible clinician and/or multidisciplinary care team.

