### Ethics and consent

Independent ethical approval has been granted by a local research ethics committee and the NHS Health Research Authority. The patients taking part in this study will have learning disabilities and be receiving inpatient care. Capacity to consent will be checked in the following ways: the Mental Capacity Act of 2005 will be followed and the patient’s responsible clinician will be advised that capacity to consent to take part in research is in the study inclusion criteria. Should there be any concern raised by the patient, their responsible clinician/care team or a member of the research team regarding capacity to consent an ‘empirical assessment of capacity to consent’ [30] will be carried out by a member of the research team. No further action will be taken if the patient is assessed to lack capacity. Patients will be initially approached by their responsible clinician or a member of their immediate care team to inform them about the study. If the patient would like further information about taking part in the study, this will be provided in written form via the study information sheet. Should patients require this information to be read aloud to them, this will be carried out by care staff who work closely with them and know them well. Patients will be given a minimum of 2 days to decide if they would like to take part in the study after receiving the study information sheet allowing them time to consider the information. Within the study information and consent form, patients will be informed that they can withdraw from the study at any time if they change their mind about participation, without penalty. If patients withdraw during the study, they will be asked if the researchers can include data collected up to that point in the study. Should they wish to proceed, they will be invited to a one-to-one meeting with a member of staff or research assistant and the study information and consent sheet will be reviewed with them and read aloud should they require this. Patients will be invited to have a member of staff who knows them well present at this meeting should they so wish. The voluntary nature of their involvement in this study and being able to withdraw from the study at any point without prejudice to further treatment will be explicitly stated on the study consent form. Recruitment of patients involved in current research or having recently been involved in research is not an exclusion criteria for participation in this study. We will not be asking potential participants to declare if they have recently been involved in research during any stage of the study.

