### Sample size

Twenty patients will be randomly assigned across both treatment allocations. The sample size for this feasibility study is limited due to a number of factors including limitations of time and budget, the intensity of the intervention, and the nature of the settings that it is taking place in. Participants are being recruited from four NHS hospitals in England with low, medium, and high levels of security. Smaller numbers of participants in multiple sites maximises the potential to assess feasibility objectives across a range of complex secure healthcare settings. This multi-site study will assist in future trial planning and inform feasibility from multi-level perspectives regarding issues and occurrences that could inform procedures related to recruitment, treatment acceptability, therapist adherence, and institutional support.

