### Data monitoring and interim analyses

A data monitoring committee will not be in place. Negative reactions and experiences of participants in the study and/or adverse clinical concerns can be raised by the participant, their responsible clinicians, or members of their immediate care team. It is an inclusion requirement that the participant’s responsible clinician and/or multidisciplinary care team support their involvement in the study and are therefore informed about the nature of the treatment being carried out.

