## Discussion

This study has been designed to establish feasibility and inform future design of a RCT to evaluate the effectiveness of manualised interpersonal art psychotherapy. Findings will inform the procedures and provide data to calculate the standard deviation of outcome measures and degrees of certainty and estimation of numbers of patients required for a future trial. Additional feasibility objectives will explore therapist adherence to the manual, study, and treatment acceptability and inform the design of a novel attentional control condition.

Potential challenges within this study include clinician’s willingness to approach patients for the study without prior knowledge of the manualised interpersonal art psychotherapy treatment. Strategies being employed to support uptake at sites include providing bespoke information to multidisciplinary teams and, where needed, specific site visits to give presentations to the wider clinical teams.

It is clear that there are a small number of evidence-based psychological treatments for people with learning disabilities [20] and it is important that feasibility work is carried out to maximise the potential for successful completion of RCTs. The study aims and objectives will support a robust assessment of feasibility and inform future trial design.

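### The counts stated for objective 1 leave out patients whose clinician and team both withhold support, so they cannot directly measure clinicians' willingness to recruit

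*Protocol article*

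**What the plan says.** Study aims and objectives gives the first feasibility objective two parts: "patients willingness to be randomised and clinicians willingness to recruit their patients into the study". Feasibility outcomes then fixes one measure for both. They "will be evaluated by assessing the number of eligible patients who were recruited at each site and the number of patients who declined", with a reference to Additional file 1, which is not among the documents at hand.

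Two other sections determine who can enter those counts. Inclusion criteria for patients requires that the patient's "involvement in the study is supported by their responsible clinician and/or multidisciplinary care team", and Data monitoring and interim analyses restates this as an inclusion requirement. Ethics and consent sets the route of contact: "Patients will be initially approached by their responsible clinician or a member of their immediate care team".

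The Discussion lists among potential challenges clinicians' "willingness to approach patients for the study without prior knowledge of the manualised interpersonal art psychotherapy treatment". It describes information for teams and site visits to support uptake, but no count of how often support was withheld.

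**The concern.** The measure counts eligible patients recruited and patients who declined, but eligibility already depends on what the clinician part of the objective is meant to assess. If neither clinician nor team supports a patient's participation, that patient fails an inclusion criterion and is not counted as eligible. Nor would the patient normally be approached, so there is no decline to count. A refusal at that step leaves no trace in either count.

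The study exists to establish whether a definitive trial is feasible, with a primary focus on implementation and acceptability. If the measure is applied as written, one of the two parts of its first objective has no direct answer. A recruited-to-eligible rate from these counts would also overstate yield if someone later applied it to a pool of patients defined by clinical criteria alone.

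**Working it through.** The protocol states no figure for uptake or clinician support, so there is nothing to reproduce. The check has two steps: follow each kind of patient through the stated definitions, then see whether the counts respond to clinician support.

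**Step 1: where each patient is counted**

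| Patient meets all other criteria and... | Eligible? | Can be recruited or decline? |
|---|---|---|
| neither clinician nor team gives support | no | no |
| clinician withholds support, team gives it | can be | yes, if the team makes the approach |
| supported but not approached | yes | no |
| supported and approached | yes | yes |

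The first row drops out of the measure altogether. The third appears only as a remainder (eligible minus recruited minus declined), and only if the number eligible is itself tabulated.

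**Step 2: do the counts respond to clinician support?**

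Inputs:
- R = 20 recruited, from Sample size ("Twenty patients will be randomly assigned across both treatment allocations").
- u = uptake among eligible patients. Assumed, shown at 50% and 80%.
- s = share of otherwise suitable patients who have clinician and/or team support. Assumed, shown from 100% down to 25%.
- All supported patients are taken to be approached.

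Formulas: eligible E = R/u; declined = E − R; otherwise suitable M = E/s; support withheld = M − E; recruited/suitable = R/M = u × s.

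With u = 50%: E = 20/0.5 = 40 and declined = 40 − 20 = 20.

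| s | M | Support withheld | Recruited/eligible | Recruited/suitable |
|---|---|---|---|---|
| 100% | 40 | 0 | 50% | 50% |
| 75% | 53.3 | 13.3 | 50% | 37.5% |
| 50% | 80 | 40 | 50% | 25% |
| 25% | 160 | 120 | 50% | 12.5% |

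With u = 80%: E = 20/0.8 = 25 and declined = 25 − 20 = 5.

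| s | M | Support withheld | Recruited/eligible | Recruited/suitable |
|---|---|---|---|---|
| 100% | 25 | 0 | 80% | 80% |
| 75% | 33.3 | 8.3 | 80% | 60% |
| 50% | 50 | 25 | 80% | 40% |
| 25% | 100 | 75 | 80% | 20% |

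In each table the protocol's counts are the same on every row. Recruited/eligible equals u and does not contain s. Its ratio to recruited/suitable is 1/s, so it is twice as high at 50% support and four times as high at 25%.

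**The case against.** The strongest objection is that the sentence fixing the measure cites Additional file 1. That file may contain a screening flow with exclusions and reasons, and an article need not repeat it. This stands as a limit on certainty. Nothing in the text shown says that withheld support is counted, however, and the measure as worded does not count it.

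A reader might also infer more than the documents support:

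- **That objective 1 cannot be answered at all.** Willingness among eligible patients can still be estimated from the recruited and declined counts, imperfectly.
- **That every clinician refusal is hidden, so support is 100% by construction.** The criterion says and/or, and a team member may make the approach. A patient whose responsible clinician alone objects may still be eligible. Only patients lacking both kinds of support must drop out.
- **That the definitive trial would be planned with too few sites.** Recruits are counted per site, and that number is already net of refusals. A later trial with the same support criterion would meet the same filter. The overstatement arises only if the recruited-to-eligible rate is multiplied by a pool that ignores the criterion, which the protocol does not propose.
- **That the protocol regards clinician reluctance as its main obstacle.** The Discussion includes it among potential challenges, ties it to unfamiliarity with the treatment, and does not rank it.
- **That the reasons for declining are wrongly left unspecified.** A split into refusal of randomisation, therapy or recording is log detail that an article may omit.

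Low recruitment at a site could hint at reluctant clinicians. It cannot be told apart from a site with few suitable patients.

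**Conclusion.** The point holds for one of the two parts of objective 1. Given the inclusion criterion and the route of approach, the stated counts do not directly measure clinicians' willingness to recruit. This follows from the protocol's own wording and needs no assumption about rates.

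The size is unknown, because the documents give neither patient uptake nor clinician support. The tables show only how the arithmetic behaves over an assumed range, and they assume that every supported patient is approached. The conclusion is also subject to what Additional file 1 contains. The change should be made because it is cheap and gives the clinician part of the objective a direct measure. No eligibility rule, treatment or sample size is affected.

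**What to change.** In Feasibility outcomes, for objective 1 only, define the denominator as patients who meet all inclusion and exclusion criteria other than clinician or team support. Report for each site the number:

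1. clinically eligible in that sense;
2. with support given or withheld, recorded separately for the responsible clinician and the team because of the and/or wording, with a brief reason when withheld;
3. approached;
4. consented or declined.

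Keep the four single-case recruits in a separate flow, since they are not randomised and say nothing about willingness to be randomised. If Additional file 1 already holds these steps, it is enough to say so in the text and name the denominator.

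The cost is extra screening-log columns, a short reason from clinicians when they withhold support, and a reported uptake that will look less favourable wherever support is withheld.
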